### Blinding

The nature of the intervention prevents blinding of outcome collectors because they can observe whether the baby receives “multisensory simulation bundles” in the NICU or not. Hence, an independent outcome-evaluation team that is not involved in the implementation of the study will be invited to assess the outcomes. This team will comprise an investigator, a physician, and two research assistants. The investigator and the physician will be responsible for interpreting the actigraphy and amplitude-integrated electroencephalography (aEEG) data, respectively. The two research assistants, with international Griffiths Mental Development Scales (GMDS) qualifications, will perform Griffiths assessments and provide evaluations. Furthermore, data analysts will be blinded to the participant allocation as much as possible.

### Randomization and allocation

The study participants will be randomly assigned to group A or B with a distribution ratio of 1:1. A statistician has prepared a computer-generated randomization list with variable block sizes. The random allocation will be concealed in serially numbered, opaque, and sealed envelopes prepared for the site.

### Screening and enrollment

The screening will be performed by the study nurses, who will approach the eligible infants once they are stable. Owing to the fragile clinical status of VPIs, the study nurse and attending doctor will continuously monitor their clinical stability during the run-in period assessment. The criteria of clinical stability will be as follows: (1) when the vital signs of the infants are within the normal range according to the Neonatology book [27], including the temperature, heart rate, respiratory rate, and blood pressure; (2) when no vasoactive drugs or cardiopulmonary resuscitation are used for infants during the run-in period. Once the run-in period assessment is complete, the study nurse will open a sealed envelope containing the study identification number and group allocation and will inform the research team (see Patient flow, Fig. 1). Additionally, the study nurse will explain the experimental protocol, processes, and precautions to the parents of infants who meet the inclusion criteria. Finally, the study nurse will obtain signed letters of informed consent from the parents.

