### Participants

This study proposes the following inclusion criteria: (1) infants who are clinically stable in a NICU, born at a minimum of 28 weeks and less than 32 weeks GA; (2) birth weight between the 10th and 90th percentiles of the average birth weight for the same GA, identified as appropriate [2]; and (3) parents agreeing to participate in the study and for follow-up diagnosis and treatment at the designated hospital for one year after discharge. The exclusion criteria will include the following: (1) congenital malformation in the infant that interferes with the intervention or for which the intervention interferes with the required care (e.g., complex congenital heart disease, complex gastrointestinal malformations, diaphragmatic hernia); (2) severe nervous system malformations or disorders (e.g., bilirubin encephalopathy, central nervous system infection, intracranial hemorrhage of ≥degree III); (3) independent predictors of disturbed sleep or neurodevelopment (e.g., inborn metabolism errors, preeclampsia, bronchopulmonary dysplasia); and (4) visual or hearing impairment. Those with the following criteria would be exited from the study: (1) terminating treatment or death during the study period or (2) adverse clinical events likely associated with receiving the multisensory stimulation bundles, or severe adverse events possibly related to the multisensory stimulation bundles.

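### As written, the allocation is revealed before parents sign consent, which does not fit the inclusion criteria and turns refusals into unbudgeted losses after randomisation

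*Protocol article*

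**What the plan says.** All references are to the protocol article.

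- **Screening and enrollment, who screens:** "The screening will be performed by the study nurses, who will approach the eligible infants once they are stable".
- **Screening and enrollment, opening of the envelope:** the trigger is "Once the run-in period assessment is complete". At that point "the study nurse will open a sealed envelope containing the study identification number and group allocation and will inform the research team". Consent is not named as a condition.
- **Screening and enrollment, explanation:** the next sentence reads "Additionally, the study nurse will explain the experimental protocol, processes, and precautions to the parents of infants who meet the inclusion criteria".
- **Screening and enrollment, consent:** the section closes with "Finally, the study nurse will obtain signed letters of informed consent from the parents".
- **Participants, inclusion criterion 3:** "parents agreeing to participate in the study and for follow-up diagnosis and treatment at the designated hospital for one year after discharge".
- **Randomization and allocation:** 1:1 allocation, variable block sizes, and numbered, opaque, sealed envelopes.
- **Interventions:** both groups receive both types of care, and allocation fixes only the order.
- **Sample size calculation:** 36 infants required, raised to 40 for 10% dropout.
- **Data collection:** data may be left out only after withdrawal from participation or for death in hospital.

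**The concern.** Sealed envelopes protect enrolment only if the decision to enter is settled before the envelope is opened. In the written order, one role screens, opens the envelope, explains the study and asks for the signature. That nurse would know whether the infant starts on the device or on standard care while seeking consent, and the parents could learn it before deciding. Who enters each sequence could then depend on the sequence.

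Two things are at stake. One is the comparability of the sequence groups. The Data analysis section treats intervention as a between-subjects factor and lists contrasts that set group A against group B, so comparability matters even in a crossover. The other is the count of infants. A family that refuses after the envelope is opened has been randomised but contributes no data, and in a trial of 40 a few such families matter. The protocol does not say how they would be handled.

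**Working it through.** **1. The order of steps.** Set side by side, the two sections give:

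| Step | Screening and enrollment | Participants |
|---|---|---|
| Run-in complete | Trigger for opening the envelope | – |
| Envelope opened, team informed | Done by the study nurse | Parental agreement should already hold, as an inclusion criterion |
| Study explained | Written after the envelope step | – |
| Consent signed | Written last, introduced by *finally* | – |

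No section states that consent is signed before the envelope is opened. Criterion 3 implies agreement before allocation, and the enrolment text places the signature after it.

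**2. The planned sample size.** Inputs from the Sample size calculation section: difference 0.04, SD 0.05, two-sided α 0.05, power 90%, stated requirement 36.

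- A parallel comparison of two means gives 33 per arm, 66 in total, which does not match.
- A 2×2 crossover, with 0.05 read as the SD in each period and no within-infant correlation, does match. The SD of the within-infant difference is 0.05 × √2 = 0.0707, so the standardised difference is 0.04 / 0.0707 = 0.566.
- Normal approximation: N = (1.960 + 1.282)² / 0.566² = 32.8. The paired t test gives 34.8, so 35, or 36 when rounded to an even number.
- Power at N = 36, by noncentral t with N − 2 degrees of freedom, is 0.909.
- Dropout: 36 / 0.90 = 40, as stated.

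The 40 is therefore used up by the 10% dropout allowance.

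**3. Effect of refusals after allocation.** The protocol gives no refusal rate, so r is assumed, with a range. Refusals are taken as equal in both sequences and not replaced.

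- Evaluable infants = 40 × (1 − r) × 0.90, rounded down.
- Number to randomise to keep 36 evaluable = 36 / [0.90 × (1 − r)], rounded up.

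| Assumed r | Evaluable of 40 | Power | Randomise to keep 36 |
|---|---|---|---|
| 0% | 36 | 0.91 | 40 |
| 5% | 34 | 0.89 | 43 |
| 10% | 32 | 0.87 | 45 |
| 20% | 28 | 0.82 | 50 |
| 30% | 25 | 0.77 | 58 |

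The counts depend only on r and the 10% dropout. The power column also depends on the crossover reading in step 2.

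**4. With consent first.** Refusals fall before randomisation, r is 0% by construction, and the planned 40 randomised and 36 evaluable stand.

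**The case against.** **The order may be loose prose.** The word that introduces the explanation to parents adds a duty and does not strictly fix a time. *Finally* may only close the pair of explaining and signing. The patient-flow figure is not available here, and criterion 3 suggests that agreement comes first. This stands as a limit: actual practice may be consent first. It does not remove the point, because the text still makes the end of the run-in the only trigger for opening the envelope and puts the signature last. If practice is sound, the section misdescribes it.

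**Concealment.** A reader might infer that the envelope system is defeated. The documents do not support that. Numbered, opaque envelopes and variable blocks hide each allocation until its own envelope is opened. The weakness lies in what happens between opening and signature.

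**The crossover softens the bias.** This stands. Every infant is due both types of care, so a family could select only on order, and within-infant contrasts are much less exposed than a parallel comparison. A reader might also infer that a first-period treatment comparison is the one most at risk, but the Data analysis section lists no such comparison.

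**Intention-to-treat.** A reader might see a contradiction with that principle. The protocol mentions it only in connection with missing values, so the handling of refusals after allocation is unaddressed rather than contradicted.

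**Replacement.** The plan is to recruit 40 from more than 100 very preterm infants a year. A refusing family could be regarded as not recruited and be replaced, in which case no shortfall follows. This stands, and it is why the losses above are conditional. Replacement would not undo selection by sequence.

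**Conclusion.** The concern holds in limited form. As written, the allocation is opened and shared before the parents' signature is obtained, and this does not fit inclusion criterion 3. If the written order is followed, entry can depend on the sequence, and refusals become losses after randomisation that the 10% allowance does not mention. The bias, if any, concerns order only and is likely to be smaller than in a parallel trial.

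The size of the loss cannot be taken from the protocol. Assumed refusal of 5% to 30%, on top of 10% dropout and without replacement, leaves about 34 to 25 evaluable infants from 40, with power of about 0.89 to 0.77. The power figures read 0.05 as the SD in each period with no within-infant correlation, which is the reading that reproduces 36.

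The documents do not show that any infant was in fact allocated before consent, or that the trial will fall short of 36.

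**What to change.** 1. Reconcile the Participants and Screening and enrollment sections. State that the study is explained, consent is signed and eligibility is confirmed before the next envelope is opened. The person taking consent then cannot know that infant's allocation.
2. Define the analysis set as all infants randomised after consent.
3. If any infant was allocated before consent, report the number of refusals in each sequence, so that readers can judge whether selection occurred.

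The cost is a wording change, a short briefing for the study nurses and one count per sequence, with no extra staff. The Trial status section gives recruitment from April 2022 and projected completion in December 2023, so reordering may reach few remaining infants. Clarifying what was done and reporting any refusals after allocation matters at least as much.

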**Fig. 1 Fig1:**
[figure not shown]
Patient flow

### Interventions with participants and investigation equipment

Participants will receive two types of care—“standard care” and “standard care plus multisensory stimulation bundles”—randomly for two consecutive weeks each (see schedule of enrollment, interventions, and assessments in Fig. 2). Thus, every participant will receive the tested intervention. The difference between the groups will only be the order in which they receive the intervention. Furthermore, all healthcare providers will receive detailed training on the study process before the study commences. To ensure precise and standard sensory stimulations, we will provide the multisensory stimulation bundles using the multisensory stimulation-supported device. The device application’s standard operating procedure (SOP) has been developed. All healthcare providers involved in VPI care will be trained to apply the device and standard care through presentations and bedside demonstrations prior to the start of the study, ensuring intervention homogeneity.

**Fig. 2 Fig2:**
[figure not shown]
Schedule of enrolment, interventions, and assessments

### Standard care

The standard care will involve specific interventions, including reducing light intensity, noise level, posture support, and pain management [21], which will be implemented according to the SOP of NICU developmental care. Moreover, infants’ conditions will be assessed at a minimum of every hour or as needed by bedside nurses.

### Multisensory stimulation bundles

Based on the Enriched Environment recommendation, the multisensory stimulation bundles will be presented in this research [19]. Specifically, two stimuli mechanisms using the multisensory stimulation device will be implemented by trained staff. This device will be able to provide (i) multisensory stimulation bundles (i.e., vision, auditory, and tactile), which simulates maternal interaction with infants, and (ii) posture support similar to the intrauterine boundary-like enclosed physical space to allow the infant’s upper and lower extremities to touch the device wall and bounce back; this physical activity and sense of boundary experience will trigger a hand-to-mouth midline orientation movement, which could promote the neurobehavioral development of infants. The intervention bundles provided with the multisensory-supported device will be included as follows (see Figs. 3 and 4).

Visual stimulation: Based on recent recommendations and evidence [18, 28], cycled light will be provided in a 12-h-on, 12-h-off pattern. Near-darkness (5–30 lux) will be provided using the designed eye mask except for procedures during night hours (7:00 PM to 7:00 AM). Meanwhile, daylight (200–600 lux) will be provided with folded incubator covers to allow light in from four sides during daytime hours (7:00 AM to 7:00 PM), which means the eye mask will be removed during this period. Moreover, the researcher will also assess lux measures for every infant weekly.Auditory stimulation: Based on the available evidence [15, 16], a vocal player will provide a recorded lullaby and maternal heartbeat for 15 min at 9:00, 12:00, and 19:00 after feeding (see Fig. 3).Tactile stimulation: A simulated tactile module has been developed based on the global massage protocol parameters [29, 30]. It aims to provide a sensation similar to parents’ gentle touch. The vibration ranges from the shoulders to the legs of the body and is produced outside the mattress. Low-frequency (18 Hz) vibration will be provided through tactile stimulation for 15 min twice a day (see Fig. 3). The frequency of vibrations is calculated according to the gesture strength of massage provided by parents or medical staff. The researcher accumulated massage strengths provided by 10 personnel (five parents and medical staff), converted them into vibration frequency, and identified the frequency intensity as 18Hz.A uterus-like boundary: This womb-simulating device allows infants to assume a similar position and movement as in the uterus. A corn-derived fiber was selected as the inner lining of the boundary. This fabric has a resilience force equal to the newborn’s maximum muscle strength to encourage their middle orientation and self-generated movements (see Fig. 4).

**Fig. 3 Fig3:**
[figure not shown]
Overall design of device

**Fig. 4 Fig4:**
[figure not shown]
Position and movement support module

### Investigational equipment

Guided by global guidelines and current evidence, a multisensory-supported device was specifically designed to provide precise and standard multisensory stimulation bundles with smooth clinical adaptation for VPIs during hospitalization. The device is composed of inner and outer skeletons connected by articulated components. Several functional buttons are set on the outer skeleton, including vocal play and head–shoulder lift. More details on the device introduction can be found in Additional file 1.

Moreover, to ensure the safety of the “multisensory-supported device” equipment design, the researchers sent the study equipment to the Chinese National Medical Device Inspection Center for testing its safety. Preclinical studies began after receiving the product safety report. During the study, participants will be continuously monitored using an electrocardiography monitor and assessed by bedside nurses at 3-h intervals or as needed as part of routine care. The study nurse will check the fidelity of intervention delivery twice daily and record it in the checklist. Additionally, there will be at least one new device on standby to promptly replace any faulty devices for the infants. Moreover, the study nurse will check the parameters (i.e., lux measures) of the device in use weekly to ensure they stay within the predetermined range. The study checklist will also record the measurement outcome.

### Study outcomes

All infants will participate in the same assessment schedule regardless of group assignment. In this study, the period of crossover intervention will be no more than 5 weeks (including the run-in period assessment).

#### Primary outcome

The primary endpoint of this study is sleep efficiency, which is defined as the average proportion of sleep time for 7 days at weeks 2 and 4 (see Fig. 2). In this study, sleep is defined as three consecutive minutes with lower-extremity movement below the threshold. It is measured using an actigraphy watch (model: Actiwatch-2). Actigraphy is a reliable and valid method for continuously recording limb movements and transferring sleep parameters [31, 32]. Data from the Sleep Watch Actigraph will be coded into sleep and wake states at 1-min intervals using Action 4 research-level software (Ambulatory Monitoring, Inc, Ardsley, New York), compatible with the actigraphy watch. Sleep/wake measures will be extracted from actigraphy data by one investigator who is blind to the infants’ assigned groups. The actigraphy watch weighs 27 grams. Previous observations made at the study institution have shown that the device has minimal impact on infants’ activities. To further minimize its impact on the activities of preterm infants, the researcher will uniformly place the watch on the infant’s thigh.

#### Secondary outcomes

Secondary study outcomes will include the following variables:Other sleep indicators: Sleep duration, fragmentation index, and amplitude of limb movement will also be obtained using the actigraphy watch (model: Actiwatch-2).Burdjalov Score: The Burdjalov Score is a scoring system used to evaluate the brain maturation of neonates. It is measured through aEEG examinations (CFM3000). It comprises four component variables: (1) presence or absence of “sleep–wake cycling,” (2) continuity of the brainwave record pattern, (3) recording bandwidth, and (4) lower-border amplitude (in μV) (see Table 1). Each variable will be independently evaluated, and each participant’s scores will be summed to determine the total score for each recording [33]. The minimum and maximum possible total scores are 0 and 13, respectively. A qualified physician will conduct bedside aEEG examinations, which involve continuous data collection over 4 h at baseline, week 2, and week 4 after randomization (see Fig. 2). Afterward, the physician will interpret the aEEG data to calculate the Burdjalov Score. During the aEEG examination, the room temperature will be maintained at 24–28°C, while unnecessary iatrogenic procedures on the infant will be minimized.The Griffiths Mental Development Scales (GMDS) with six subtests will be used to assess neurodevelopment in children aged 0–2 years [34, 35]. Each subtest measures a different development area: (A) locomotor, (B) personal–social, (C) hearing and language, (D) eye and hand coordination, (E) performance, and (F) practical reasoning. The mental age (MA) is derived by calculating the average raw scores of the six subtests. The corrected age (CA) is calculated as the difference between the examination and birth dates. The developmental quotient (DQ) is expressed as a mental ratio, i.e., DQ = (MA / CA) × 100. Finally, the total development quotient is represented by GQ, which represents the average value of all the development quotients [35]. The scale is culturally appropriate for Chinese children [35]. In this study, two physician research assistants with international GMDS qualifications will conduct GMDS assessments on study participants. Furthermore, the assessment process will be video-recorded for possible replay. Interrater measurement consistency will be obtained prior to the actual assessment of infants to reduce errors.Growth indicators at follow-up will include weight, length, and head circumference. Moreover, the research assistant will collect data when participants return for follow-up at 3, 6, and 12 months of CA.

**Table 1 Tab1:** The Burdjalov Score

Score	Continuity	Sleep-wake cycling	Amplitude of lower border	Bandwidth span and amplitude of lower border
0	Discontinuous	None	Severely depressed (<3 µV)	Very depressed: low span (≤15 µV) and low voltage (5 µV)
1	Somewhat continuous	Waves first appear	Somewhat depressed (3–5 µV)	Very immature: high span (>20 µV) or moderate span (15–20 µV) and low voltage (≤5 µV)
2	Continuous	Not definite, somewhat cycling	Elevated (>5 µV)	Immature: high span (>20 µV) and high voltage (>5 µV)
3		Definite cycling, but interrupted		Maturing: moderate span (15–20 µV) and high voltage (>5 µV)
4		Definite cycling, noninterrupted		Mature: low span (<15 µV) and high voltage (>5 µV)
5		Regular and mature cycling		

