## Methods/design

### Study design and setting

This study was designed as a prospective, evaluator-blinded, randomized crossover trial, in accordance with the Standard Protocol Items: Recommendations for Interventional Trials guidelines. This study is conducted in the neonatology department of Shanghai Children’s Medical Center, a pediatric tertiary teaching hospital, and the National Children’s Medical Center in China. The study protocol has been approved by the Hospital Research Ethics Committee (approval number: SCMCIRB-K2021086-1) and is registered in the Chinese Clinical Trial Registry (Registry Number: ChiCTR2200059099).

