### Data collection

All data collection collaborators will receive detailed training on the study process before starting the study to ensure the homogeneity and integrity of data collection. During the hospital stay, outcome measurements will be conducted by reviewing medical records, including medical notes and nursing care charts, as well as using the Actiwatch-2 Actigraph, aEEG, and GMDS for data collection. Further, The data collectors must have obtained the necessary licenses, such as aEEG and GMDS qualifications. Data collected after withdrawal of participation and the participants’ hospital mortality would be the only reasons for the non-inclusion of data. All forms completed by the outcome measurement, screening, and enrollment teams will be entered into an electronic platform; and two staff members will work together on data entry to minimize input mistakes. The Epi Data software will be used to control the range and accuracy of the data entered. The schedule for outcome assessments is shown in Fig. 2.

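### The Blinding and Secondary outcomes sections conflict on who reads the aEEG, so blinded scoring of the Burdjalov Score at weeks 2 and 4 is not secured

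*Protocol article*

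**What the plan says.** All references are to the protocol article.

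- **Study design and setting** describes a "prospective, evaluator-blinded, randomized crossover trial".
- **Blinding** begins with a concession: "The nature of the intervention prevents blinding of outcome collectors because they can observe whether the baby receives" the bundles. The remedy is that "an independent outcome-evaluation team that is not involved in the implementation of the study will be invited to assess the outcomes". The team has one physician, and roles are assigned: "The investigator and the physician will be responsible for interpreting the actigraphy and amplitude-integrated electroencephalography (aEEG) data, respectively".
- **Secondary outcomes**, on the Burdjalov Score, says: "A qualified physician will conduct bedside aEEG examinations, which involve continuous data collection over 4 h" at baseline, week 2 and week 4. It continues: "Afterward, the physician will interpret the aEEG data to calculate the Burdjalov Score".
- **Primary outcome** states that the investigator who extracts the actigraphy measures does not know the infants' assigned groups. There is no matching statement for the aEEG reader.
- **Data collection** adds: "The data collectors must have obtained the necessary licenses, such as aEEG and GMDS qualifications".
- **Data analysis** puts the primary and secondary outcomes into the same linear mixed-effect model. Only the follow-up indicators are left untested.

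**The concern.** The blinding rests on separating the people who see the infant from the people who judge the outcome. For the aEEG, the outcome description appears to join the two roles again. The bundle is delivered through an enclosing device, with an eye mask at night and incubator covers folded open by day. A physician who runs a 4-hour bedside recording would normally see which care the infant is receiving, and nothing says the device is removed or hidden for the examination.

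In a crossover, a reader's expectation acts directly on the within-infant contrast between care conditions, and randomising the order does not remove it. A difference in the Burdjalov Score could then partly reflect how the traces were read, and the evaluator-blinded label would not cover this outcome.

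**Working it through.** The protocol gives no figure to reproduce on this point. The finding comes from comparing sections; the arithmetic only shows how much a reading bias could matter.

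**1. Who records and who reads**

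| Question | Blinding | Secondary outcomes |
|---|---|---|
| Who is at the bedside for the aEEG? | Outcome collectors, who cannot be blinded | A qualified physician |
| Who interprets the aEEG? | The physician of the independent team | The physician, referring back to the one just introduced |
| Are traces coded or masked? | Not stated | Not stated |

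The Secondary outcomes section introduces one physician for the aEEG. If that is the team physician, the independent reader is also a bedside collector, whom the Blinding section says cannot be blinded. If two physicians are meant, the Secondary outcomes wording does not say so. Either way the sections need reconciling.

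**2. How much of the score is judgement (Table 1)**

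- Continuity: maximum 2, verbal categories.
- Sleep-wake cycling: maximum 5, verbal categories.
- Lower-border amplitude: maximum 2, µV cut-offs.
- Bandwidth: maximum 4, µV cut-offs.

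Verbal: 2 + 5 = 7. Voltage-based: 2 + 4 = 6. Total: 13, which matches the stated maximum.

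**3. Which readings are exposed**

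The week-2 and week-4 readings. The baseline reading presumably precedes any intervention.

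**4. Sensitivity to a reading bias**

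From the document: n = 36 (Sample size calculation, before the dropout allowance) and a two-sided 5% level. Assumed, because the document gives neither: an SD of within-infant score differences of 1.5 to 3 points, and a mean reading bias b of 0.1 to 0.5 point in favour of one condition, with no true effect. The paired t test is a simplification of the planned mixed model.

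The noncentrality is δ = b × √36 / SD = 6b / SD. The false-positive rate is P(|T| > t₀.₉₇₅), with T noncentral t on 35 df and critical value 2.030.

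| b (points) | SD 1.5 | SD 2 | SD 3 |
|---|---|---|---|
| 0.1 | δ = 0.40: 7% | δ = 0.30: 6% | δ = 0.20: 5% |
| 0.25 | δ = 1.00: 16% | δ = 0.75: 11% | δ = 0.50: 8% |
| 0.5 | δ = 2.00: 49% | δ = 1.50: 31% | δ = 1.00: 16% |

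Using 34 df, as a two-sequence crossover analysis would, gives the same whole percentages.

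**The case against.** A reader might infer that the Burdjalov Score is definitely read unblinded. The documents do not go that far. No sentence says so; it follows from putting two sections together. Read with the Blinding section, the physician who interprets could be the team physician while another physician records, and masking of stored traces is an operational detail that an article may leave to the full protocol. This limits the certainty but does not remove the point: the article itself states who records and who reads, and on its plain wording that conflicts with its own safeguard. Being outside the implementation of the study is also not the same as being unaware of the care given.

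A reader might also take the whole score to be subjective, or the 49% to be an expected error rate. Neither is supported. Six of the 13 points have voltage cut-offs, and the 49% needs a 0.5-point bias with the smallest assumed SD. At 0.1 point the inflation is negligible.

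It is also tempting to say that existing staff could simply take over the recording. The Data collection section requires aEEG qualifications of data collectors, but it does not establish that a qualified collector other than this physician exists. Recruitment began in April 2022 with completion projected for December 2023, and the article appeared in November 2023, so reassigning the recordings could by then affect few infants.

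Finally, this is one secondary outcome. The primary outcome has a reader stated to be blind and software-coded sleep and wake states.

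**Conclusion.** The concern holds as a conflict between two sections. As written, the week-2 and week-4 Burdjalov Scores can be read by someone who has seen the care condition, so evaluator blinding is not secured for this tested, partly judgement-based secondary outcome. That rests on the plain reading that one physician both records and scores, and on the absence of any stated masking.

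Actual bias is possible, not shown, and its size is unknown. Under the assumptions above, the false-positive rate for this outcome would lie anywhere from about 5% to 49%. The primary outcome and the sample size are unaffected. The point is worth correcting because the correction is cheap.

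**What to change.** 1. Amend the aEEG text under Secondary outcomes to agree with Blinding, stating who records and who scores.
2. Store each aEEG trace under a code, with infant identity, date, week and care condition removed. Have the existing evaluation-team physician score the traces in random order, in a batch after the week-4 recordings. Traces already scored can be re-scored in this way.
3. Where an aEEG-qualified collector is already available, have that person make the bedside recording instead of the scoring physician. Otherwise, report that the reader attended the recordings and do not describe this outcome as fully evaluator-blinded.

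Cost: protocol wording, some coding work, and scores that become available later. Step 2 needs no new staff. It reduces recognition of the infant and condition but cannot rule it out if the reader was at the bedside, which is why step 3 asks for disclosure in that case.
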